### Blinding

The allocation of individual participants to treatment groups will be concealed to the chief investigator up until the point of a participant commencing treatment. Individual participants will not be told their group allocation until the completion of their involvement in the trial. All participants allocated to the placebo intervention group will have the opportunity to receive the NET treatment free of charge at the completion of their initial participation. No other incentives will be given for a participant's involvement or follow-up.

Any primary care providers (e.g. endocrinologist) will be blinded to the participant's group allocation. As the practitioners involved in the study will be performing both the NET treatment and the placebo intervention, it will be necessary for the group allocation to be disclosed to these practitioners. Practitioners will be instructed to perform the placebo with the same gusto as the NET treatment. The treating practitioners will have no previous role in the diagnosis or management of the participant's thyroid condition.

Group allocation will be concealed from the pathology company involved in the collection and analysis of the serum outcome measures. Statisticians involved in the analysis of the trial data will be blinded to group allocation.

### Protocol

Participants will be randomly allocated to either a treatment group (NET) or a placebo group. Both groups will receive ten interventions (either NET or placebo) during the initial 6 weeks of the trial period. Two interventions will be administered in the first four weeks followed by one intervention per week in the remaining two weeks.

### NET Protocol

Neuro-Emotional Technique was developed by Walker [21] in 1985, and can be summarised as a 15-step, multi-modal intervention that incorporates principles from several health disciplines, including; chiropractic, biology, cognitive behavioural psychology, and Traditional Chinese Medicine (TCM)[22]. A brief description of the NET procedure is described below. It is important to note that the procedure is based on many different theories. Some of these theories have been well researched, while others have not undergone the same scientific scrutiny.

The NET procedure is specifically designed to detect and remove a specific type pathophysiological/syndromal pattern called a Neuro Emotional Complex (NEC). Walker postulates that the presence of NECs has a negative influence on an individual's physiology, and that by removing NECs using NET, physiological homeostasis may be promoted [21].

Walker defines the NEC as a subjective maladaption syndrome adopted by the organism in response to a real or perceived threat to any aspect of its survival [21]. Walker states that the NEC/syndromal pattern will contain the aspects listed below:

1)A facilitated or inhibited muscle; 2) A specific active Meridian Access Point (MAP); 3)An imbalance in a meridian, and an active pulse point or MAP point; 4) A specific emotion; 5) A cathected and often recallable memory picture (Snap Shot) of a past significant emotional event; 6) A conditioned response with a resistance to extinction, and a predisposition for stimulus generalization; 7) A vulnerability to suppression, repetition-compulsion and reaggravation/restimulation causing a cyclical reinforcement; and 8) A specific subluxation or sequence of spinal subluxations.

The protocol uses manual muscle testing (MMT) to aid the practitioner in finding and removing NECs. A muscle test in which the individual is unable to withstand a standardised test pressure is termed an inhibited/weak (w) test. A muscle test in which an individual is capable of withstanding a standardised test pressure from the practitioner is termed a facilitated/strong (s) test [21]. Strong and weak test outcomes are used to provide feedback for the practitioner throughout the protocol. The specific steps of the protocol and the muscle testing outcomes at the various steps are outlined in the appendix (See Additional File 2) [21].

There are two methods used in NET to detect the presence of an NEC. The two types are defined by Walker as a Mind-Entry (ME) and a Body-Entry (BE). The ME is used to detect the presence of an NEC by having the patient either think of a situation/memory/feeling or by verbalising specific statements [21,23]. The BE method of detecting an NEC involves having the patient or practitioner touch specific cutaneous areas on the body recognised in TCM to be related to the presenting condition. NET is based on the notion that there will be demonstrable changes in a patient's physiology when a salient ME or BE is employed. Manual muscle testing (MMT) is used to demonstrate the physiological change associated with the NEC [21]. For convenience, the anterior deltoid muscle test is most commonly used during the NET procedure [21].

Walker states that NET engages the energetic system of the body as described by TCM. In TCM, it is thought that there are 12 main channels throughout the body that carry vital energy - termed *chi*. These channels are called meridians. Disruption to the flow of chi along a meridian channels is believed to result in disease and ill health [24]. It is postulated that elements of the NEC are stored within this energetic network. Walker opines that an NEC stored within the meridian system can be accessed via cutaneous points associated with the meridians (See Additional File 3 &4) [21] and MMT [21].

According to the Five Element Theory of TCM, each of the meridians is associated with specific emotions. For example, the liver meridian is said to be associated with the emotion of Anger [25]. An exaggerated experience of emotion (either too much, too little, or prolonged experience of a specific emotion) can cause disruption to the free flow of chi through the meridians. The normal experience of emotion is not pathological, but extremes of emotion are thought to cause disharmony within the meridian system [24,25]. Walker and others have expanded upon this concept and created tables to which NET practitioners can refer to during the NET protocol (See Additional File 5) [21]. It is thought that NECs are created during times (past or present) in which a person is experiencing physiological or meridian deficit [21].

The NET procedure is therefore designed to find NECs that are purported to be having a negative influence on an individual's physiological and energetic system. The energetic imbalance accompanying the NEC will have a related emotion and a recallable memory picture/snap shot that is associated with that emotion. Using the NET protocol in combination with MMT, the specific emotion and its associated snap shot are detected.

It is thought that the NEC may fail to resolve under normal circumstances and can become a conditioned response that is subject to restimulation/reaggravation in reaction to a variety of different stimuli. For this reason, NET is thought to aid in the extinction of classically conditioned responses to traumatic emotional stimuli [18].

Walker states that there will be specific spinal regions that will require treatment for each type of meridian imbalance (See Additional File 5).

Once an appropriate BE or ME has been found, a specific meridian imbalance, a specific emotion, and a recallable snap shot have been displayed, a practitioner can proceed with the corrective phase of the technique. The corrective procedure involves having the individual think of the original snap shot and the associated emotion, while at the same time holding the corresponding MAP point (See Additional File 4)[21]. The practitioner then applies a light, bilateral tapping to specific spinal regions on breathing [21].

The original snap shot and the original BE or ME are then tested to assess the adequacy of the treatment.

During the intervention phase, the trial practitioners will seek to find and remove any NECs that may be present in the trial participants using NET.

It is important to note that the version of NET to be used in this study (12-step protocol) does not represent the NET system in its entirety. The 12 Step protocol utilises Steps 1-11, and Step 15. The originators of NET champion the combined use of manual therapy, nutritional supplementation and homeopathic treatment in addition to addressing the psychosocial aspects of a patient's presentation [21]. For research purposes, the initial three aspects mentioned above (manual therapy, nutrition, and homeopathy) and steps 12-14 of the NET protocol will be omitted to limit the number of confounding variables, and ensure a more accurate interpretation of the results. The protocol to be used in this research will be similar to that employed in previous research papers describing NET as a treatment modality [16,26-31]. Karpouzis et al published a similar protocol for the use of NET for Attention Deficit Hyperactivity Disorder in an open access journal in 2009 [16].

### Placebo Protocol

The placebo protocol will align clearly with the NET protocol however the purported therapeutic components of the NET procedure will be removed and replaced with innocuous steps (See Additional File 6.)

### Measures

The standard guidelines for the assessment of individuals with thyroid dysfunction will be used by the primary care providers to establish the diagnosis of hypothyroidism [1]. The primary and secondary outcome measures (DASS, SF-36v2 and Serum Measures) will be applied pre-intervention to obtain baseline data, then reapplied at six weeks (post-intervention) and six months (study conclusion). Measurement of basal heart rate and basal temperature will be applied for each day of the six month study period, and will commence one week prior to the research intervention.

### Primary Outcome Measures

Significant proportions of individuals with 'managed' hypothyroidism continue to experience many of the symptoms associated with the overt, untreated version of the condition [1]. Depression is a common symptom associated with primary overt hypothyroidism [1]. Hypothyroid patients are more likely to experience constitutional and neuropsychiatric complaints as compared to euthyroid individuals [12]. For this reason, the primary outcome will involve the measurement of Depression using of the Depression Anxiety Stress Scale (DASS). The DASS is an instrument for measuring the negative states of depression, anxiety and stress. It is constructed of three self-report scales that enable researchers and clinicians to more concisely define, understand and measure these three clinical states. Each of the three scales contains 14 items that assess different aspects of depression, anxiety and stress [32].

The questionnaire is used to determine negative emotional states versus negative emotional traits. The DASS is based on a dimensional concept of psychological disorder. For this reason, the DASS is not used to allocate patients to specific diagnostic categories. This concept is different to other classificatory systems such as the Diagnostic and Statistical Manual of Mental Disorders (DSM) and International Classification of Diseases (ICD).

All items are rated on a four-point Likert scale from 0 - 3. Scores are determined according to how often particular symptoms were experienced in the past week, with high scores indicating a higher frequency of symptoms. Depression represents a sum of scores from 14 items within the DASS pertaining to depression [32]. States of dysphoria, hopelessness, devaluation of life, self-deprecation, anhedonia, inertia and a lack of interest and involvement are assessed by the 'depression' specific questions within the DASS. Normative data for the Depression scale of the DASS describes a mean of 6.34 with a standard deviation of 6.97. Clinically, depression scores between 0-9 are considered normal. Scores of 10-13 and 14-20 indicate mild and moderate states of depression respectively. Severe and extreme states of depression are defined by scores between 21-27 and 28+ respectively [32].

The DASS questionnaire will be issued to each participant at the specified times; study commencement, six-weeks and six-months. The results will be collected and forwarded to the chief investigator for compilation and scoring using relevant scoring algorithms and software [32].

Improvements in the negative emotional state of depression will be represented by decreased scores by respondents at 6 weeks and at 6 months. The associated anxiety and stress scores from the DASS will be included in the secondary outcome measures.

### Secondary Outcome Measures

The secondary outcome measures (from serum analysis) are listed in Table 1. All blood collection and analysis will be performed by the commercial pathology laboratory DHM. The pathology company DHM provides pathology services to general practitioners, medical specialists, nursing homes, private hospitals and researchers [33].

**Table 1 T1:** Serum Secondary Outcome Measures

Test Name	Abbreviation	Reference Range
Thyroid Stimulating Hormone	TSH	0.40 - 4.00 mU/L
Free Thyroxine	FT4	9.0 - 19 pmol/L
Free Triiodothyronine	FT3	2.6 -6.0 pmol/L
Thyroglobulin auto-antibodies	Anti-Tg	0 - 80 IU/ml
Thyroid Peroxidase auto-antibodies	Anti-TPO	0 - 120 IU/L

Participants will be issued with a blood sample request form that can be used at any DHM collection centre. Blood samples will be obtained at the beginning of the trial, then again at the six week and six month points. Participants will be instructed to provide a blood sample that will be used to measure a variety of thyroid related indicators (See Table 1). There will be no specification regarding timing or fasting for the sample collection. The initial blood sample will completed one week prior to the first treatment in both groups. Blood samples will be spun in gel tubes at the collection centre before being couriered in cold storage to the central DHM laboratory for analysis. At the central laboratory, the ARCHITECT^® ^assay kits (Chemiluminescent Microparticle Immunoassay) will be used to measure the TSH, FT3, FT4 in the serum samples (Abbott Laboratories, Abbott Park, IL, USA). Immulite^® ^2500 will be used to quantify levels of anti-thyroid peroxidase antibodies and auto-antibodies to thyroglobulin in serum. The Immulite^® ^2500 method involves a solid-phase, enzyme labelled, chemiluminescent sequential immunometric assay (Siemens, Los Angeles, CA, USA). All results will be forwarded to the chief investigator for monitoring, compilation and analysis.

It is anticipated that the majority of participants will be receiving treatment in the form of L-Thyroxine supplementation. For this reason, serum measures of TSH, serum FT4, serum FT3 should fall within normal reference ranges (See Table 1) provided there are no major alterations to this existing treatment strategy. In adequately treated participants, the addition of the experimental intervention should not influence serum thyroid hormone levels. However, in individuals who are not being medicated, or in individuals who are being under-treated upon entry into the trial, a decrease in TSH measurements and an increase in FT4 and FT3 measurements may be expected during the course of the trial.

In individuals who are being over-treated, elevated FT4 and FT3 levels and decreased TSH measurements will be demonstrated at baseline. It is expected that there will be no change in the serum measures in this subgroup.

It is unclear how the autoimmune markers will respond to the addition of NET to any existing treatment regimens.

In addition to the serum measures, participants will fill out the SF-36v2 and the additional items (anxiety and stress) of the DASS.

The SF-36v2 health survey is a questionnaire used to assess outcomes in eight different domains: role limitations because of physical or emotional problems, physical and social functioning, bodily pain, perception of mental and general health, and vitality [34].

Improvements in functional health and well-being as measured by the SF-36v2 will be depicted by increased scores by the respondents at six weeks and at six months. Deterioration in functional health and well-being will be revealed by a decrease in SF-36v2 scores.

Two additional secondary outcome measures are to be completed and recorded by participants at home for each day of the six month trial period are listed below:

Basal Heart Rate (BHR)

Basal Temperature (BT)

After signing up to take part in the trial, participants will be given a home diary, digital thermometer and instructions on how to record their BHR and BT. Participants will be instructed to make an effort to perform these measurements at the same time each day, and ideally before getting out of bed in the morning. For BHR measurements, participants will be instructed to find their radial pulse and then record the number of beats that occur in one minute and record this figure in the diary provided.

Due to the chronotropic effect of the thyroid hormones on heart rate, untreated or undertreated individuals will demonstrate lower heart rates at baseline. It is anticipated that if NET therapy has a positive influence, there may be a trend over time toward slight increases in heart rate.

Basal temperature recording will be performed using a digital thermometer placed under the axilla. The thermometer will be placed under the axilla for approximately two minutes and the resultant temperature reading recorded.

Due to the thermogenic action of thyroid hormones, it is hypothesised that unmedicated or under-treated participants will experience an increase over time in basal temperature that may approach normal ranges of basal temperature (35.5 - 37.0°C) with the addition of NET treatment [35]. Adequately treated individuals should display normal basal temperatures at baseline that remain unperturbed by any additional treatment.

The secondary measures of basal heart rate and temperature measurement to be employed in this research study are commonly used by thyroid specialists as a crude measure of thyroid performance that is adjunctive to the hormone assays [36-38].

The recording of BHR and BT will begin one week prior to the initial intervention and continue for each day of the clinical trial.

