### Statistical Analysis

Two-sample t-tests will be used to compare change from baseline for NET treatment versus control at each of six weeks and six months for the primary outcome measure. Linear mixed-effects models will be used examine change over time in the treatment and placebo groups for the basal temperature and basal heart rate groups as well as the other secondary outcome measures. A significance level of 5% will be used throughout the analysis. Because the analyses will be seen as hypothesis generating, no adjustment for multiple testing will be used. The R software program [39] will be used to conduct the analyses. Complete case analysis will be employed for participants who strictly followed the trial protocol. Sensitivity analysis will be used for withdrawals, missing data and participants who violate the study protocol eg. changes in medication during the study period. This will be done using imputation techniques including last value carried forward, and multiple imputation.

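### Leaving the time of day of the three blood draws open adds avoidable error to the secondary TSH, FT4 and FT3 comparisons: a loss of precision, not a bias, and of unknown size

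*Protocol article*

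**What the plan says.** The rule is in the protocol article under Secondary Outcome Measures: "There will be no specification regarding timing or fasting for the sample collection". It is a stated choice, not a detail left to a fuller document. The same section fixes the visits: "Blood samples will be obtained at the beginning of the trial, then again at the six week and six month points", and "The initial blood sample will completed one week prior to the first treatment in both groups". The word timing in the rule is therefore best read as time of day. The place is also free: "Participants will be issued with a blood sample request form that can be used at any DHM collection centre".

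Three other statements bear on the point:

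- On medication, the section says: "It is anticipated that the majority of participants will be receiving treatment in the form of L-Thyroxine supplementation".
- On the expected signal, it says: "In adequately treated participants, the addition of the experimental intervention should not influence serum thyroid hormone levels". No change is expected in over-treated participants either. Change is foreseen only in unmedicated or under-treated participants.
- On the home measures of heart rate and temperature, it says: "Participants will be instructed to make an effort to perform these measurements at the same time each day".

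Statistical Analysis assigns linear mixed-effects models to the home measures "as well as the other secondary outcome measures", which includes the serum markers. It names no adjustment for draw time.

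**The concern.** The serum outcomes are judged by change within a person over three draws. If a hormone level depends on the hour of the draw or on the interval since a tablet, and these differ between one person's draws, the difference enters the error term. Heart rate and temperature are recorded daily, so timing error there partly averages out. With only three blood samples there is little averaging.

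Precision matters somewhat more here because the protocol itself expects serum change in only part of the sample, so the pooled effect is diluted. What is at stake is how well the trial can estimate change in three secondary hormone outcomes. The comparison of arms stays valid, and the primary outcome is a questionnaire score that does not depend on the blood draw.

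**Working it through.** **The plan's own figure.** The only computed sample size is for DASS depression: a difference of 4, SD 8, one-sided 5%, 80% power. The normal approximation gives n = 2 × (1.645 + 0.842)² × (8/4)² = 49.5, so 50 per group. The t-test version gives 50.15, rounded up to the stated 51. The figure reproduces but does not concern the serum outcomes, for which the document states no SD, target difference or power.

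**Inputs for the serum outcomes.** None of these is in the documents, so all are assumptions:

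- w: the within-person SD of a serum value apart from timing
- t: the SD of the timing effect, with r = t/w
- c: the correlation between the timing effects of one person's draws, taken between 0 (times chosen afresh each visit) and 1 (always the same hour)

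**Variance of a change between two draws.**

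- With timing effects removed: 2w²
- With free timing: 2w² + 2t²(1 − c)
- Ratio: V = 1 + r²(1 − c)

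**Power.** Take a hypothetical serum comparison with 80% power, two-sided 5%, when timing effects are absent. With free timing, power = Φ((0.842 + 1.960)/√V − 1.960).

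Worked at r = 0.5:

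- c = 0: V = 1 + 0.25 = 1.25, √V = 1.118, and 2.802/1.118 − 1.960 = 0.546, so power is 71%.
- c = 0.5: V = 1 + 0.125 = 1.125, √V = 1.061, and 2.802/1.061 − 1.960 = 0.681, so power is 75%.

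| r | V, c = 0 | power, c = 0 | V, c = 0.5 | power, c = 0.5 |
|---|---|---|---|---|
| 0 | 1.00 | 80% | 1.00 | 80% |
| 0.25 | 1.06 | 78% | 1.03 | 79% |
| 0.5 | 1.25 | 71% | 1.125 | 75% |
| 1 | 2.00 | 51% | 1.50 | 63% |

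The smallest detectable difference grows by √V, so by 6% to 12% at r = 0.5.

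**How to read the table.** These are upper limits on what a fix could recover, because a preferred time of day would not remove all timing variation. The formula is for a change score between two draws. The planned mixed models use all three draws, but timing variation enters their residual error in the same way.

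**The case against.** The strongest objection is that the premise lies outside the documents. Nowhere do they say that TSH, FT4 or FT3 vary with clock time or tablet interval, and r could be close to zero. This stands: the size is unknown, and the table only shows what follows if such variation exists.

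Other points that stand:

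- People with fixed routines tend to attend at similar hours, which is why c belongs in the formula. Setting it to 0 gives the worst case.
- The 80% starting power is hypothetical for any serum outcome.
- Dilution by participants in whom no change is expected is the larger obstacle to a pooled serum effect, and timing control does nothing for it. Tablet-interval variation cannot arise in unmedicated participants, one of the two groups in which change is foreseen.
- The contrast with the home measures is suggestive only. Those are basal readings, ideally taken before rising, so the hour is part of what is measured. A reader might infer that the protocol contradicts itself, and it does not.
- A rigid time window could do harm. Statistical Analysis restricts the complete case analysis to participants who adhered strictly to the protocol, so an out-of-window draw could remove someone from the DASS analysis as well.
- The text cites a 2009 publication in the past tense, while recruitment is dated September 2006 to March 2010. At least 27 of about 42 months had passed, so many draws were probably already taken.

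Free attendance at any centre is a defensible pragmatic choice. That does not answer the remaining point: the protocol does not provide for recording the draw time or for using it in the analysis, although both would cost little.

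**Conclusion.** The point holds as a modest, low-priority one. The protocol expressly leaves time of day open, and any dependence of the three hormones on draw time or tablet interval becomes avoidable within-person error. If r = 0.5 and c lies between 0 and 0.5, change-score variance rises by at most 12.5% to 25%, and a hypothetical 80% power falls to about 75% to 71%. Both r and c are assumed.

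Three stronger readings are tempting, and the documents support none of them:

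- **Bias.** Allocation is random, and participants and the laboratory are blinded to it, so timing variation should be similar in both arms.
- **A serum signal that timing noise would readily swamp.** The documents give neither the signal nor the noise. The fall to about one half in the table needs r = 1 and unrelated draw times.
- **Damage to the main result.** DASS depression and its sample size are unaffected. The outcomes concerned are secondary, in a pilot whose analyses are declared exploratory.

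**What to change.** Replace the sentence on timing with a request that each participant attend at about the same time of day for all three draws where practicable, with no change to anyone's medication. In addition:

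1. Record draw time and time of last tablet on the request form.
2. Use both as covariates in the serum mixed models, or in a sensitivity analysis of them.
3. State that a draw at another time is not a protocol violation and does not remove the participant from the complete case analysis.
4. For draws already taken, use collection times where they were logged.

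The cost is one line and two entries on an existing form. The downside is minor inconvenience to participants and incomplete adherence to the preferred time, so some timing variation will remain.

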The treatment of individuals with hypothyroidism typically follows a biomedical paradigm. There are clearly defined biochemical boundaries for what constitutes the clinical manifestation of hypothyroidism and standard algorithms to guide the commencement and progression of treatment. Several studies however have reported inadequate treatment (as determined by thyroid blood markers) in a significant proportion (20%) of individuals with 'managed' hypothyroidism [8,9]. Saravanan *et al *report that substantial numbers of hypothyroid sufferers continue to experience the plethora of hypothyroid symptoms despite demonstrating hormone levels within reference ranges [10].

Whybrow *et al *state that almost 100% of severe hypothyroid sufferers are found to have significant concurrent depression [11]. Grozinsky-Glasberg *et al *state that hypothyroid patients are more likely to have a decreased sense of well-being and more commonly experience constitutional and neuropsychiatric complaints as compared to euthyroid individuals [12]. Practitioners must take care when initiating treatment for hypothyroidism in certain populations (ischemic heart disease, adrenal cortical insufficiency) and be mindful of avoiding adverse drug interactions [1].

After an exhaustive search of the medical literature it would appear that little consideration has been given to the concept of a biopsychosocial-based management approach to this condition. Within the chiropractic profession there are anecdotal reports and case studies [13] to suggest that a biopsychosocial-based treatment approach may be applicable to hypothyroidism. This manuscript has been compiled to outline the methodology for a randomised-controlled clinical study investigating a biopsychosocial approach to primary overt hypothyroidism that adheres to the CONSORT [14] checklist in its design.

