### Power analysis and sample size justification

A (one-sided) power analysis indicated 51 subjects per group will yield an 80% chance of detecting a decrease in depression scores of at least four points in treatment compared to control using a standard deviation of eight based on simulation. Clinically, a four point reduction in depression scores, as defined by the DASS, would represent a meaningful reduction in depressive states. A four point decrease may indicate that an individual has gone from expressing moderate to mild states of depression or mild to normal expression of depressive states [32].

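### For TSH, FT4, FT3 and basal temperature the plan expects change only in unmedicated or under-treated participants, but the stated analysis only compares the randomised groups as a whole, which dilutes that effect, often severely

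*Protocol article*

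**What the plan says.** All statements are in the protocol article.

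- **Who is enrolled.** The Sample section admits people under any management, including none. Secondary Outcome Measures adds: "It is anticipated that the majority of participants will be receiving treatment in the form of L-Thyroxine supplementation". It concludes that TSH, FT4 and FT3 should then lie in the Table 1 ranges.
- **Predicted serum response.** "In adequately treated participants, the addition of the experimental intervention should not influence serum thyroid hormone levels". No serum change is expected in over-treated participants either. A fall in TSH and a rise in FT4 and FT3 may be expected in those who are unmedicated or under-treated.
- **Predicted temperature response.** A rise is hypothesised in the unmedicated or under-treated, whereas "Adequately treated individuals should display normal basal temperatures at baseline that remain unperturbed by any additional treatment".
- **Other measures.** For heart rate, the article says that untreated or under-treated people start lower and that a slight rise may follow. It does not say that adequately treated people will show none. It calls the response of the auto-antibodies unclear.
- **Analysis.** Statistical Analysis applies linear mixed-effects models, by treatment and placebo group, to temperature and heart rate "as well as the other secondary outcome measures". It names no term, stratum or subgroup for baseline thyroid status. It calls the analyses hypothesis generating and makes no multiplicity adjustment.
- **Blood sampling.** "There will be no specification regarding timing or fasting for the sample collection". For temperature and pulse, participants are asked to aim for the same time each day.

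**The concern.** The article makes an explicit prediction of effect modification: baseline thyroid status decides who can change on four secondary outcomes. The one comparison it states ignores that factor. If the prediction is right, the group contrast is a weighted average of a real effect in a minority and zero in everyone else.

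The stake is interpretation. A null pooled result on TSH or temperature would probably be read as no influence of the intervention on thyroid function. Yet on the plan's own reasoning such a result is likely, for moderate effects, whether or not the under-treated respond. It would therefore say little about the second objective (short- and medium-term response on the secondary outcomes). Choosing the subgroup or its cut-off after seeing several thyroid measures, with no multiplicity control, would be hard to defend, so the choice is better fixed beforehand.

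**Working it through.** **1. The plan's own figure.** Power analysis and sample size justification reads: "A (one-sided) power analysis indicated 51 subjects per group will yield an 80% chance of detecting a decrease in depression scores". The difference sought between the groups is 4 points, with SD 8. The standardised effect is 4/8 = 0.5. A one-sided 5% two-sample t-test needs 50.15, so 51 per arm, and 51 per arm gives 80.6% power. The figure reproduces. It concerns the depression score only; no power is stated for any secondary outcome.

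**2. Inputs for the dilution check.**
- n = 51 per arm, from the power section.
- Significance level 5%, from Statistical Analysis. Sidedness of the secondary tests is not stated; two-sided is used here.
- Effect zero in non-responders, as Secondary Outcome Measures predicts.
- Responsive share f: not given, so assumed over 0.10 to 0.49. The nearest figure is the 20% of managed patients reported as inadequately treated (Background). It may include over-treated people and leaves out the unmedicated.
- Effect d in responders, in SD units: not given, so assumed over 0.5 to 1.5.
- No dropout, a common within-group SD, and a single post-baseline comparison.

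**3. Formulas.** Pooled effect = f × d. Responders and non-responders mixed in the treated arm add variance, so the averaged variance is 1 + f(1 − f)d²/2 and the standardised pooled effect is f × d / √[1 + f(1 − f)d²/2]. Subgroup size per arm = 51f, rounded down. Power is from the noncentral t.

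Example, f = 0.20 and d = 1.0: the pooled effect is 0.20 SD. The variance is 1 + 0.16/2 = 1.08, so the standardised effect is 0.20/1.039 = 0.192. Power is 17.0% without the extra variance and 16.1% with it. The subgroup has 51 × 0.20 = 10.2, so 10 per arm, and power 56.2%.

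**4. Results (two-sided 5%).**

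| f | d | Pooled effect (SD) | Pooled power, without / with mixture variance | Subgroup n per arm | Subgroup power |
|---|---|---|---|---|---|
| 0.10 | 1.0 | 0.10 | 7.9% / 7.8% | 5 | 28.6% |
| 0.20 | 0.5 | 0.10 | 7.9% / 7.9% | 10 | 18.5% |
| 0.20 | 1.0 | 0.20 | 17.0% / 16.1% | 10 | 56.2% |
| 0.40 | 1.0 | 0.40 | 51.6% / 47.2% | 20 | 86.9% |
| 0.40 | 1.5 | 0.60 | 85.1% / 75.9% | 20 | 99.6% |
| 0.49 | 1.5 | 0.735 | 95.7% / 90.1% | 24 | 99.9% |

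The first row is also the case in which half of the 20% are over-treated.

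**5. The same from the other side.** With 51 per arm the pooled test has 80% power at 0.56 SD. The responder effect must then be 0.56/f: 5.6 SD at f = 0.10, 2.8 at 0.20, 1.87 at 0.30, 1.40 at 0.40 and 1.14 at 0.49, ignoring the mixture variance. At f = 0.20 and d = 1.0, a pooled test with 80% power would need 394 per arm.

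**6. Not modelled.** Daily temperature readings may reduce error variance. A larger SD in untreated participants, which is plausible for TSH, would lower the subgroup power shown.

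**The case against.** **Only a journal article is at hand.** It lists no fixed effects, and nothing in it excludes a baseline-status term; an analysis plan not shown could hold one. That is fair. The point rests instead on what the article does fix: a prediction for a defined part of the sample, and a stated comparison that does not address it. For the same reason the log scale is a recommendation; the article does not say that TSH will be analysed untransformed.

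**The first objective concerns the whole sample,** and the group comparison answers it. This stands, and is why the all-participant estimate should stay.

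**The outcomes are secondary, unpowered and hypothesis generating.** This limits the weight of the point, but an exploratory analysis should still be aimed at the hypothesis it explores.

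**Stronger readings that the article does not support.**
- A reader might infer that any real effect falls below detection. It does not: pooled power is 76-90%, mixture variance included, for a 1.5 SD effect in a 40-49% share.
- A reader might extend the point to heart rate or the antibodies. The article makes no prediction of zero effect for heart rate in adequately treated people, and none of any kind for the antibodies.
- A reader might take 20% as the share with TSH above the Table 1 limit. It is not that figure.
- A reader might want a TSH cut-off alone to define the main effect of interest. That would drop unmedicated participants with TSH in range, whom the article names, and rest the main result on perhaps 5-10 per arm.

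**Conclusion.** The point holds for TSH, FT4, FT3 and basal temperature. The stated hypothesis and the stated comparison do not match, and a null pooled result would not test that hypothesis. The size depends on two quantities the article does not give. At an assumed 20% share and 1.0 SD effect, pooled power is about 16-17%, against about 56% in a subgroup of 10 per arm. The subgroup is no cure for small numbers: power is about 29% with 5 per arm at 1.0 SD, and about 19% with 10 per arm at 0.5 SD. The gain is therefore more in interpretability than in power. The depression outcome and the 51 per group are unaffected.

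**What to change.** 1. Keep the all-participant estimate for TSH, FT4, FT3 and basal temperature.
2. For these four outcomes, prespecify an arm-by-baseline-thyroid-status term in the mixed model. Define status as unmedicated or baseline TSH above the Table 1 limit of 4.00 mU/L, versus the rest. Report the effect in each stratum, and the difference between strata, with confidence intervals and labelled exploratory.
3. Analyse TSH on the log scale, so that a few very high values do not dominate.
4. As a minor, separate precision point, ask each participant to give the three blood samples at about the same time of day. Sample timing adds noise to both arms alike and is not part of the dilution argument.

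**Cost.** Items 1 to 3 need only analysis wording and data already collected; item 4 needs one line on the blood request form and helps only samples not yet taken. The downside is wide intervals. With 10 and 41 per arm in the two strata, the standard error in SD units is √(2/10) = 0.45 for the responsive-stratum effect and √(2/10 + 2/41) = 0.50 for the difference between strata. Conclusions should therefore rest on the intervals and not on an interaction p-value. Randomisation is not stratified on thyroid status, so the small stratum may also be unbalanced by chance.
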